#### Secondary outcomes analysis

Continuous outcomes (CRPS severity score, FMA, MBI, infrared thermography ΔT, and rs-fMRI connectivity) will be analyzed using the same LMM specification as the primary outcome.

Ordinal outcomes (Brunnstrom stages and MAS) will be analyzed using generalized estimating equations (GEE) with a cumulative logit link function.

Categorical outcomes (e.g., AE adverse event causality) will be compared using *χ*^2^ or Fisher’s exact test.

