#### Baseline

The general condition of eligible participants, including demographic and clinical characteristics, such as age, weight, and disease treatment history, will be recorded in the CRF. The research assistants will conduct the primary and secondary outcomes assessment before the first session of treatment.

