#### Primary outcome analysis

Pain intensity, measured based on the VAS, will be analyzed using a linear mixed-effects model (LMM). Fixed effects will include group, time, group-by-time interaction, baseline VAS score, and rescue medication use. Random effects will account for participant-specific intercepts. Between-group differences at each time point will be estimated with 95% confidence intervals (CIs). A reduction of ≥1.5 points from baseline will be considered clinically meaningful. Pre-planned contrasts will be conducted to test the following hypotheses: (1) the experimental group (YLDJJ + rTMS) will be superior to control group 2 (sham acupuncture + rTMS); and (2) the experimental group will be superior to control group 1 (conventional acupuncture + rTMS). These comparisons will directly test the specific efficacy of YLDJJ acupuncture with those of both a sham control and a conventional acupuncture active control.

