#### Exploratory and safety analyses

Blinding success will be assessed using Bang’s BI with 95% CIs. The incidence of AEs will be compared using *χ*^2^ tests, and the severity of AEs will be analyzed via GEE.

Rescue medication use will be included as a covariate in all primary and secondary analyses. Sensitivity analyses will exclude high-frequency users (>3 doses per week).

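### Read literally, the continuous secondary outcomes are adjusted for baseline pain and not for their own baseline value

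*Protocol article*

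**What the plan says.** The Primary outcome analysis section lists the terms of the linear mixed model for pain: "Fixed effects will include group, time, group-by-time interaction, baseline VAS score, and rescue medication use". It adds that "Random effects will account for participant-specific intercepts", and it asks for group contrasts at every visit. The model's one baseline term is the baseline of its own response, VAS.

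The Secondary outcomes analysis section then takes five continuous outcomes (CRPS severity score, Fugl-Meyer, modified Barthel, thermographic temperature difference and resting-state connectivity) and says that they "will be analyzed using the same LMM specification as the primary outcome".

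Two other places change the covariates. Descriptive statistics adds pre-stroke hand dominance for outcomes such as the Barthel index. Exploratory and safety analyses states: "Rescue medication use will be included as a covariate in all primary and secondary analyses". Neither adds or substitutes an outcome's own baseline.

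The own baselines will exist. The Baseline section states: "The research assistants will conduct the primary and secondary outcomes assessment before the first session of treatment". Table 4 also ticks the baseline column for each of these outcomes.

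**The concern.** For VAS the specification is sound, because the response is adjusted for its own starting value. Carried over word for word, the response changes to Fugl-Meyer, Barthel or connectivity while the covariate stays baseline pain. A patient's starting value on a scale is usually a much better predictor of the later value on that scale than a pain score is. The plan as worded would therefore collect the useful covariate and adjust for a weaker one.

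Two things are at stake. The first is precision, in a trial sized on VAS with 33 evaluable patients per arm. The second is reproducibility of the analysis: one analyst following the text and another following its presumed intent would fit different models and could report different estimates. A prespecified model should not leave that choice open.

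**Working it through.** The article states no figure that depends on this point, so there is nothing to reproduce. The finding rests on reading the four analysis sections together; the arithmetic only shows the scale.

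**Inputs from the article.** 42 randomised and 33 evaluable per arm (Sample size); two-sided alpha 0.05 (Statistical methods).

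**Assumed inputs.** Correlation r between an outcome's baseline and its follow-up value; correlation v between baseline VAS and that follow-up value; standardised effect d = 0.5; Fugl-Meyer SD 10 to 20 points; one follow-up visit; equal SDs at baseline and follow-up.

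**1. Residual variance.** Adjusting for a covariate with correlation c leaves a fraction 1 − c² of the variance.

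| Covariate | c | 1 − c² | Removed |
|---|---|---|---|
| Own baseline | 0.5 | 0.75 | 25% |
| Own baseline | 0.8 | 0.36 | 64% |
| Baseline VAS | 0.1 | 0.99 | 1% |
| Baseline VAS | 0.3 | 0.91 | 9% |

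**2. Own baseline against VAS.** The ratio is (1 − r²)/(1 − v²).
- r = 0.7: 0.51/1.00 = 0.51 with v = 0, and 0.51/0.84 = 0.61 with v = 0.4.
- r = 0.3, v = 0.4: 0.91/0.84 = 1.08, so there is no gain.

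**3. Power.** Normal approximation: Φ(d/√(2(1 − c²)/33) − 1.96).
- Baseline VAS only: 0.53 at v = 0 and 0.60 at v = 0.4.
- Own baseline: 0.57 at r = 0.3, 0.65 at 0.5, 0.81 at 0.7 and 0.92 at 0.8.

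**4. Chance imbalance.** The standard error of the baseline difference between two arms of 42 is SD × √(2/42) = 0.22 SD. Left unadjusted, an imbalance reaches the follow-up contrast multiplied by r. A one-standard-error imbalance therefore shifts the contrast by 0.11 SD at r = 0.5, 0.15 SD at 0.7 and 0.17 SD at 0.8. On Fugl-Meyer the baseline standard error is 2.2 to 4.4 points, and the shift is 1.1 points (SD 10, r = 0.5) to 3.5 points (SD 20, r = 0.8). This is not a further cost on top of item 1: the unadjusted standard error already contains it.

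**5. Would another reading of the response supply the adjustment?**
- *Baseline kept as a response row.* With unconstrained group, time and group-by-time terms and complete data, and leaving the covariates aside, the contrast at a visit is the difference in raw means at that visit. The extra row does not adjust it.
- *Change from baseline as the response.* Own baseline is then subtracted. The relative variance is 2(1 − r) for change against 1 − r² for adjustment: 1.00 against 0.75 at r = 0.5, and 0.40 against 0.36 at r = 0.8. Most of the loss goes at high r, but not all of it.

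**The case against.** The strongest reply is that the phrase means the same model form. The primary model adjusts VAS for its own baseline, so the natural counterpart for Fugl-Meyer adjusts Fugl-Meyer for its own baseline. That reading is reasonable, and nothing shows a decision to leave own baselines out. A reader might infer such a decision, but the text does not go that far. What remains is that the covariate is named as the VAS score, and that the authors did spell out a covariate change where they wanted one (hand dominance).

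A second reply is that the Primary outcome section puts the focus on mean change from baseline, which could bring own baseline in through the response. That sentence concerns VAS only. Carried over, it would reduce the loss without removing it.

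Three stronger readings should be resisted:
- *That the ordinal models ignore baseline.* The article says only: "Ordinal outcomes (Brunnstrom stages and MAS) will be analyzed using generalized estimating equations (GEE) with a cumulative logit link function". That sentence lists no model terms, not even group or time. A condensed article may leave those to a fuller document, so no omission can be inferred.
- *That the estimates would be biased.* Allocation is randomised, so the cost is precision.
- *That a baseline imbalance passes in full into the result.* It carries over only in proportion to r.

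**Conclusion.** The point holds for the five continuous secondary outcomes and no further. As written, their models carry baseline pain as the only baseline covariate, and nothing elsewhere in the article corrects this. The consequence is lost precision and unadjusted chance imbalance, not systematic bias. The primary analysis is unaffected.

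I am confident about the wording and less so about the size, since every correlation and SD used here is assumed. The loss is substantial where the own-baseline correlation is 0.5 or more, as is plausible for motor and daily-living scales. It may be negligible where that correlation is near 0.3, which cannot be ruled out for thermography or connectivity. The change should be made, but the trial does not stand or fall on it.

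**What to change.** In Secondary outcomes analysis, qualify the sentence on continuous outcomes so that it reads: *the same LMM specification, with the baseline value of the outcome being analysed in place of baseline VAS*.

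The cost is one clause. The baseline values are already scheduled, so no visit, measurement or patient is added. The change should be made before unblinding, so that the choice of covariate cannot be linked to results.

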#### Exploratory and safety analyses

Blinding success will be assessed using Bang’s BI with 95% CIs. The incidence of AEs will be compared using *χ*^2^ tests, and the severity of AEs will be analyzed via GEE.

Rescue medication use will be included as a covariate in all primary and secondary analyses. Sensitivity analyses will exclude high-frequency users (>3 doses per week).

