#### Control group 2: sham acupuncture + rTMS

Acupuncture technique:

Acupoint selection: The same set of 12 acupoints used in the experimental group will be used for the control group.

Sham needling technique: The non-penetrating Streitberger-type placebo needle (Asiamed) will be applied at each acupoint (36, 37). This device has a blunt tip that retracts into the handle upon contact with the skin, allowing insertion without piercing the skin. The needle will be fixed in place with an adhesive ring to mimic the appearance of a real needle.

Simulated deqi: To maintain blinding, the acupuncturist will gently manipulate the sham needle handle periodically without applying penetrating pressure and will ask open-ended questions about sensation, not mentioning specific deqi sensations.

Needle retention: The sham needles will remain in place for 30 min, matching the retention time in the active acupuncture groups.

Treatment schedule: The session frequency and duration (once daily, 20 sessions) will be identical to the other groups.

rTMS Procedure:

The rTMS protocol (parameters, site, and schedule) will be identical to that described for the experimental group.

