#### Adverse events (AEs)

The safety profile will include AEs recorded following CTCAE v5.0. AE analysis will focus on incidence, severity, and causality (classified as definite, probable, or possible).

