#### AE reporting and harms

AE documentation will follow CTCAE v5.0 for all events. Specific procedures for managing common AEs are as follows: For acupuncture, minor bleeding or hematoma will be managed with prolonged local pressure; syncope (needle fainting) will be managed by immediately withdrawing needles, placing the participant in a supine position, and monitoring vital signs. For rTMS, headaches will be managed with rest and non-opioid analgesics if necessary (recorded as rescue medication); in case of a seizure (despite excluding high-risk participants), stimulation will be stopped immediately, standard seizure first aid will be administered, and medical support will be sought. Expected AEs based on the literature and our pilot data include mild (19, 41), transient headache with rTMS (~10 to 15% incidence), and minor local bleeding/bruising with acupuncture (~5 to 10% incidence). For the primary safety analysis, the focus will be on clinically significant risks by including only grade ≥2 (moderate to severe) AEs. Serious adverse events (SAEs) will be events causing death, permanent/significant disability, permanent organ damage, or hospitalization/prolonged stay. In case of SAEs, researchers will immediately ensure participant safety and report it to the sponsor and ethics committee within 24 h. The trial center and blinded editor will jointly perform emergency unblinding due to SAEs. Researchers will determine the need for further treatment using unblinded information.

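### The adverse-event causality test compares the mix of ratings among events, not risk per randomised participant, and the severity GEE does the same if it is run on events only

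*Protocol article*

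**What the plan says.** All of this is in the protocol article.

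- **Adverse events (AEs)** names three dimensions: "AE analysis will focus on incidence, severity, and causality". The causality scale has three levels: "causality (classified as definite, probable, or possible". No level is listed for an unrelated event or for no event.
- **Secondary outcomes analysis**: "Categorical outcomes (e.g., AE adverse event causality) will be compared using" χ² or Fisher's exact test.
- **Exploratory and safety analyses**: "The incidence of AEs will be compared using" χ² tests, "and the severity of AEs will be analyzed via GEE". The unit of the severity analysis (event, participant or participant-visit) is not given.
- **AE reporting and harms** sets the primary safety analysis by "including only grade ≥2 (moderate to severe) AEs". It expects mild, transient headache with rTMS in about 10 to 15%, and "minor local bleeding/bruising with acupuncture (~5 to 10% incidence".
- **Control group 2** uses a placebo needle, "allowing insertion without piercing the skin". All three arms receive the same rTMS.

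**The concern.** The randomised safety question is whether a participant assigned to YLDJJ is more likely to be harmed, or harmed more seriously, than one assigned to sham or conventional acupuncture. A causality rating exists only for an event that happened. A χ² on the three ratings tests whether the split between definite, probable and possible is the same across arms, given an event. That set of events forms after randomisation, so the comparison is no longer protected by it. If one arm had twice as many related events with the same split, the test would sit at its null.

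There is also an independence problem. χ² and Fisher's test need independent entries. Each participant has 20 sessions, the same reaction can recur, and nothing limits the table to one entry per participant.

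Severity raises the same issue if the GEE is run on events. Headache can occur in every arm, but bleeding is expected mainly where needles penetrate. The arms can then differ in event mix when the risk of a moderate or severe event is the same.

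**Working it through.** The article gives no figure for the AE analyses, so there is none of its own to reproduce beyond the arm size: 33 / (1 − 0.20) = 41.25, rounded up to 42 per arm, as stated.

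**1. Causality: who can enter the table.** The levels are definite, probable and possible. A participant with no AE fits none of them. For causality, the event-conditional reading follows from the stated levels.

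**2. Causality: repeated events.** Assumptions, none of them in the article: no true difference, 20% of participants affected (42 × 0.20 = 8.4 per arm), rating probabilities 0.3 / 0.4 / 0.3, and 1 + Poisson(m − 1) events per affected participant, so the mean is m. The three-arm by three-level table has 4 df and a 5% critical value of 9.49.

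With within-participant correlation ρ, the statistic is inflated by about D = 1 + ρ(E[e²]/E[e] − 1), where E[e²] = m² + m − 1. The rejection rate is about P(χ²₄ > 9.49/D) = exp(−x/2)(1 + x/2), with x = 9.49/D.

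- m = 1.5, identical ratings (ρ = 1): D = 2.75/1.5 = 1.83, x = 5.18, rate about 27%. Simulation: 26 to 27%.
- m = 2, identical ratings: D = 5/2 = 2.5, x = 3.80, rate about 43%. Simulation: 43%.
- m = 1.5, each rating with an even chance of being the participant's shared one (ρ = 0.25): D = 1 + 0.25 × 0.83 = 1.21, x = 7.85, rate about 9.7%. Simulation with ratings repeating half the time: 9.5%.
- One event per participant: no inflation (simulation 4.6%).

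**3. Severity, if run on events.** Let h be the headache rate in both arms, b the bleeding rate with YLDJJ (assumed 0 with sham), and g_h and g_b the shares of each that are grade 2 or higher. The article does not give g_h or g_b.

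- Share of events at grade 2 or higher, YLDJJ: (h·g_h + b·g_b)/(h + b). Sham: g_h.
- Share of participants, YLDJJ: 1 − (1 − h·g_h)(1 − b·g_b). Sham: h·g_h.

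At the midpoints, h = 0.125 and b = 0.075:

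| g_h, g_b | Events: YLDJJ vs sham | Participants: YLDJJ vs sham |
|---|---|---|
| 20%, 0% | 0.025/0.20 = 12.5% vs 20% | 2.5% vs 2.5% |
| 20%, 20% | 0.040/0.20 = 20% vs 20% | 4.0% vs 2.5% |
| 10%, 20% | 0.0275/0.20 = 13.75% vs 10% | 2.7% vs 1.25% |

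Over the full stated ranges, the YLDJJ event share is 10 to 15% in the first row and 12.5 to 15% in the third. The event comparison shows YLDJJ as milder with equal participant risk in row one, hides a higher participant risk in row two, and shows YLDJJ as more severe in row three.

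**4. How often an event-level test would reject in the row-one situation.** This uses a Pearson χ² on events as a stand-in for the GEE, 12.5% headache, and grade 1 bleeding at 5 / 7.5 / 10% with YLDJJ only.

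- 10% of headaches grade 2: 2.0 / 2.9 / 3.6%.
- 20% of headaches grade 2: 4.4 / 5.4 / 7.2%.
- 40% of headaches grade 2: 7.6 / 9.7 / 12.5%.

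The excess over 5% is nil or slight unless a large share of headaches is grade 2.

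**The case against.** Three stronger readings are tempting, and the article does not support them.

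*Both tests are run among events.* For severity this is an inference. AEs are scheduled at four visits in Table 4, and GEE is used elsewhere for repeated ordinal outcomes. A participant-by-visit grade that includes none would fit the sentence equally well, and a statistical analysis plan that is not shown may fix the unit. This stands, so the severity part is conditional. It does not rescue the causality test, whose levels are fixed in the article.

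*The plan cannot see a rise in harm.* It can. The same sentence compares incidence. If AEs tripled from 12.5% to 37.5% with the same grade mix, a pairwise incidence χ² at 42 per arm would have 78% power, against about 5% for an event-only severity test and 76 to 77% for worst grade per participant. At the article's own expected rates the incidence test is weak: any AE in 14.5 to 23.5% with YLDJJ against 10 to 15% with sham gives 7 to 21% power.

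*YLDJJ looks milder than sham by construction.* It does not. The direction depends on a grade mix that the article does not give, as the table above shows. The expected headache is itself described as mild, and the primary safety analysis drops grade 1 events.

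It is also fair to say that these tests sit among the exploratory and safety analyses, that no decision rule hangs on them, and that type I error of 66 to 84% needs a mean of 3 to 5 identically rated events per affected participant, for which the article gives no basis.

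**Conclusion.** The point holds in a limited form. The causality comparison, as its levels are defined, is conditional on an AE having occurred and is not a comparison of risk between randomised arms. Its p-value is invalid when participants contribute repeated, correlated events: about 9.5% to 27% type I error at a mean of 1.5 events per affected participant, and nominal with one event each. These rates rest on assumed event counts and rating patterns.

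The severity GEE shares the conditional comparison only if its records are events, which is not stated. In that case the result can mislead in either direction, usually by a small amount at the expected rates. The incidence test and the grade 2 or higher primary safety analysis contain the damage without correcting these two tests. This is a cheap improvement to the safety analysis and not a threat to the trial's main conclusion.

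**What to change.** In Secondary outcomes analysis and in Exploratory and safety analyses:

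1. Replace the causality χ² with the proportion of randomised participants who have at least one AE rated as related to study treatment. Give the risk difference with 95% CI for YLDJJ vs sham and for YLDJJ vs conventional acupuncture. State which ratings count as related and how an unrelated event is recorded; if all three listed levels count and no other exists, this proportion equals any-AE incidence.
2. Analyse severity as the worst CTCAE grade per randomised participant, with 0 for no AE.
3. List event-level grade and causality distributions by arm descriptively, without tests.

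This changes wording only. It uses AE data already collected and needs no extra participants or procedures. The downside is that event-level p-values are dropped.

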#### Subgroup and sensitivity analyses

Subgroup analyses will be conducted based on stroke type (ischemic vs. hemorrhagic) and baseline NIHSS score (≤8 vs. >8). Sensitivity analyses will include comparisons between ITT and PP populations and the use of non-parametric alternatives if model assumptions are violated.

#### Software and reporting

All analyses will be conducted using R software (v4.5.0) and the packages lme4, mice, and geepack. All results will be reported as statistical estimates with 95% confidence intervals, along with effect sizes for statistically significant outcomes. The false discovery rate will be used for multiple comparison adjustment in secondary outcomes.

#### AE reporting and harms

AE documentation will follow CTCAE v5.0 for all events. Specific procedures for managing common AEs are as follows: For acupuncture, minor bleeding or hematoma will be managed with prolonged local pressure; syncope (needle fainting) will be managed by immediately withdrawing needles, placing the participant in a supine position, and monitoring vital signs. For rTMS, headaches will be managed with rest and non-opioid analgesics if necessary (recorded as rescue medication); in case of a seizure (despite excluding high-risk participants), stimulation will be stopped immediately, standard seizure first aid will be administered, and medical support will be sought. Expected AEs based on the literature and our pilot data include mild (19, 41), transient headache with rTMS (~10 to 15% incidence), and minor local bleeding/bruising with acupuncture (~5 to 10% incidence). For the primary safety analysis, the focus will be on clinically significant risks by including only grade ≥2 (moderate to severe) AEs. Serious adverse events (SAEs) will be events causing death, permanent/significant disability, permanent organ damage, or hospitalization/prolonged stay. In case of SAEs, researchers will immediately ensure participant safety and report it to the sponsor and ethics committee within 24 h. The trial center and blinded editor will jointly perform emergency unblinding due to SAEs. Researchers will determine the need for further treatment using unblinded information.

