#### Quality control

Before its implementation, the trial protocol will be subjected to independent expert review, including experts in acupuncture rehabilitation, orthopedics, biostatistics, clinical methodology, etc., to ensure its scientific validity. All researchers will receive mandatory training covering patient screening, standardized acupuncture techniques, and EDC operations to ensure consistent operations. Independent auditors will conduct regular on-site supervision, verifying the protocol’s implementation, randomly selecting 10% of the clinical report forms for review, and promptly reviewing AE records. The EDC platform will be employed to ensure data quality through detailed modification audit records, automatic logical checks for outliers, and role-based access control to prevent unauthorized editing. Additionally, a three-level data monitoring committee will be established to ensure data integrity and participant safety. The primary monitor will be responsible for real-time program supervision during the intervention period; the secondary monitor (ethics and compliance experts) will review informed consent documents, track AES following CTCAE v5.0 standards, and ensure timely reporting of serious AEs to the TSC. The tertiary monitor (biostatisticians and data managers) will verify the dataset through double-entry validation and automated logical checks, resolve discrepancies, and ensure compliance with the pre-defined statistical analysis plan.

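### The serious adverse event definition has no life-threatening or medically important criterion, so an rTMS seizure that resolves without admission, prolonged stay or significant disability is not assured expedited reporting or a mandatory stop

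*Protocol article*

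**What the plan says.** The section AE reporting and harms gives the definition: "Serious adverse events (SAEs) will be events causing death, permanent/significant disability, permanent organ damage, or hospitalization/prolonged stay". For an SAE, the researchers must "report it to the sponsor and ethics committee within 24 h". The same section deals with seizure under rTMS: "in case of a seizure (despite excluding high-risk participants), stimulation will be stopped immediately". It then adds first aid and a call for medical support, but does not classify the event or set a reporting deadline. It also links unblinding to seriousness: "The trial center and blinded editor will jointly perform emergency unblinding due to SAEs".

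Two other sections depend on the SAE label. Criteria for discontinuation of the intervention requires an immediate stop when the investigator attributes an SAE to acupuncture or rTMS. Quality control has the secondary monitor "track AES following CTCAE v5.0 standards, and ensure timely reporting of serious AEs to the TSC".

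Other safeguards do not depend on the label. "AE documentation will follow CTCAE v5.0 for all events", and Quality control provides for "promptly reviewing AE records" by independent auditors. On supervision it says: "The primary monitor will be responsible for real-time program supervision during the intervention period". The discontinuation criteria also allow a stop for confirmed clinical deterioration or at the investigator's discretion. The exclusion criteria remove people with a history of epilepsy or with intracranial hypertension.

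**The concern.** The definition looks only at certain outcomes of an event. It does not ask how dangerous the event was while it lasted, or whether it is medically important for another reason. Seizure is the rTMS harm for which the article writes an emergency procedure, and it can end without any of the listed outcomes. Followed exactly, the plan would then treat it as an ordinary adverse event. The bodies that oversee safety would have no assured prompt notice, and whether later rTMS sessions go ahead would rest on clinical judgement and not on the linked-SAE rule. All three arms are exposed, because all receive the same rTMS protocol.

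**Working it through.** This is mainly a check of text. The only arithmetic describes exposure.

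1. **Is the definition closed?** It names four kinds of outcome, introduces none of them as an example, and refers to no fuller definition.

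2. **Does another section widen it?** The other places that deal with adverse events are Criteria for discontinuation of the intervention, Adverse events (AEs), Quality control, Secondary outcomes analysis, and Exploratory and safety analyses. Some use the SAE term and others deal only with recording, grading, causality or comparison. None adds a life-threatening or medically important criterion, and none ties a CTCAE grade to SAE status or to the 24 h report.

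3. **Apply the definition to a seizure that ends in the treatment room or after brief observation, with no significant disability:**
   - death: not met;
   - permanent or significant disability: not met;
   - permanent organ damage: not met;
   - admission or longer stay: not met.

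   As written, this event is not an SAE. A life-threatening event that resolves in the same way gives the same result.

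4. **What follows from the missing label?**

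| Step | Section | Applies to this event? |
|---|---|---|
| Report to sponsor and ethics committee within 24 h | AE reporting and harms | Not assured |
| Inclusion in SAE reporting to the TSC (no fixed deadline) | Quality control | Not assured |
| Mandatory stop if linked to treatment | Criteria for discontinuation of the intervention | Not assured |
| Stimulation stopped at the time, medical support sought | AE reporting and harms | Yes |
| CTCAE recording, review of AE records, supervision during the intervention period | AE reporting and harms; Quality control | Yes |
| Discretionary stop, or stop for confirmed deterioration | Criteria for discontinuation of the intervention | Available, by judgement |

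   Stopping stimulation during a seizure is management of that event. The text does not say whether the rTMS course may resume.

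5. **Exposure.** Participants planned: 126 (Sample size). Sessions per participant: 20 (Table 2). Planned rTMS sessions: 126 × 20 = 2,520. The article gives neither a seizure rate nor the share of seizures that resolve without admission, so an expected count in the gap cannot be derived.

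**The case against.** The best opposing case has several parts.

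- **The article cites no SAE standard and does not contradict itself.** This is correct, and the point does not rest on an outside norm. It rests on the article planning for a seizure while giving that event no assured reporting route.
- **Many seizures would qualify anyway.** The trial runs in a hospital and medical support must be sought, so admission is plausible. The disability criterion covers significant as well as permanent disability, so a substantial but reversible deficit could already count. This stands and narrows the gap. A reader might infer that any seizure without lasting harm falls outside the definition, and the wording does not support that.
- **No TSC deadline is lost.** This stands. A reader might infer that the event loses a deadline for each of three bodies, but the 24 h limit names only the sponsor and ethics committee. Quality control asks for timely TSC reporting and sets no fixed time for any SAE.
- **Protection does not depend on the label.** The safeguards are real, and even the mandatory stop needs the investigator to make the causal link. A reader might infer that a seizure would go unrecorded or that treatment would simply continue. The documents do not support that either. Still, none of these safeguards sets a reporting deadline or a stop rule for a seizure that resolves.

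It might also be said that a condensed article leaves such detail to the full protocol. That does not answer the point, because the article states the definition and states it as a closed list.

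**Conclusion.** The concern holds in a limited form. A seizure or life-threatening event that resolves without admission, prolonged stay or significant disability is not assured the 24 h report, inclusion in SAE reporting to the TSC, or the mandatory stop when linked to treatment. This rests on reading the four-outcome list as closed and on no other section of the article widening it.

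The severity is minor. Such events are likely to be few, given the exclusions and the events that already qualify through admission or significant disability. Their number cannot be computed from the article. The 2,520 sessions measure exposure, not harm.

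The point concerns participant safety only. A reader might infer that the safety comparison is distorted, but all events are recorded and the primary safety analysis selects by grade (2 or higher), not by seriousness. The efficacy analyses are likewise unaffected.

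**What to change.** In AE reporting and harms, add two criteria to the SAE definition: *life-threatening events* and *other medically important events, including any seizure*. The 24 h report, the SAE reporting to the TSC and the linked-SAE stop then apply without changes elsewhere.

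Because that section ties emergency unblinding to SAEs, a wider definition alone could lead to unnecessary unblinding. Add a sentence that emergency unblinding is done only when knowing the acupuncture arm would change the participant's care. rTMS is the same in all three arms, so the allocation says nothing about rTMS exposure. This second sentence offsets a side effect of the first change and does not correct a separate defect.

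The cost is two short edits, a few more expedited reports, and a rule-based stop for a participant whose seizure is linked to treatment. That participant stays in the intention-to-treat analysis, which includes everyone randomized. The wider definition adds no unblinding of its own only if the second sentence is adopted too.
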